### Statistical analysis

Preliminary analyses will summarize baseline characteristics of AGYW, MF, and peer leaders, generate frequencies (proportion) for categorical variables, medians (interquartile range) for continuous variables, and summary statistics of predictor, outcome, and mediating/moderating variables to screen and clean the data. We will evaluate randomization integrity by examining the distribution of baseline characteristics between randomization groups (i.e., AGYW assigned to ZAIMARA versus HP, peer leaders assigned to ZAIMARA versus HP, and peer leaders assigned to screening (mental health distress versus nutrition/exercise). We will adjust for potential confounders not balanced at baseline. We will examine if AGYW and peer leaders who complete the follow-up assessments differ systematically at baseline from those lost to follow-up. We will evaluate correlations among the variables, inspect scale reliabilities, and create summary scores. We will use models with random intercepts to account for clustering (if needed) and test the significance of clustering of subjects within groups and within sites.

**Aim 2**. The primary analysis will be based on the intention-to-treat population. We will use a two-sided z-test with unpooled variance to test the inequality of the proportion of HIV testing uptake at 6-months among AGYW who receive ZAIMARA compared to AGYW who receive HP. We will use log-binomial generalized linear model to estimate the effect of ZAIMARA on proportion with HIV testing uptake at 6-months, adjusting for potential confounders. Likelihood p-value < 0.05 will be considered statistically significant. We will evaluate the intervention effect on secondary *binary* outcomes (e.g., PrEP uptake, incident STI) in an analogous way. We will perform subgroup analyses, using test of interaction [78, 79] to evaluate if the effect of ZAIMARA on the primary outcome (HIV testing) differs systematically depending on hypothesized variable, such as mental health (e.g., depression, anxiety). We will include interactions between treatment condition and subgroup covariates in the generalized linear model, and obtain effect estimates, 95% confidence intervals, and p-values. For *continuous* secondary outcomes (e.g., HIV/STI knowledge score), we will evaluate the effect of ZAIMARA using linear regression models.

**Aim 3.** We will summarize baseline characteristics of peer leaders by group using frequency and proportion for categorical variables while median and interquartile interval will be used for continuous variables. The primary analysis will be based on a comparison of the proportion of peer leaders retained in their positions, defined as present at 6 months; never absent without leave, between the mental health distress screening and referral versus nutrition and exercise screening groups using two-sided z-test with unpooled variance. All analyses will be performed using Stata 18 MP8 (StataCorp, College Station, TX, USA). We will assess mental health at baseline and end of term for both groups.

**Aim 4.** We will estimate the implementation outcomes for the ZAIMARA intervention. We will summarize all scales using mean score and standard deviation. We will calculate the mean response across items for each implementation outcome, separately for each group of respondents. We will calculate overall adoption rate as number (%) of sites and MoH staff intending to adopt ZAIMARA. We will evaluate fidelity to ZAIMARA by calculating the percentage in which the peer leaders adhered to the curriculum (e.g., 80%) and how competent they were based on mean ratings.

Qualitative data will be evaluated using thematic analysis with a phenomenological approach. We will record, transcribe, and enter transcripts into NVivo (NVivo qualitative data analysis software; QSR International Pty Ltd. Version 12, 2018). We will format analytical memos and oversee development of the codebook based on determinants in the Implementation Research Logic Model (IRLM) and EPIS phases. Research assistants will complete analytical memos after each IDI/FGD to iteratively inform the next round of data collection. Through periodic assessment for thematic saturation, two study qualitative analysts will finalize the codebook containing deductive codes arising from the IRLM (e.g., inner setting) and inductive codes that emerge from the data (e.g., cultural taboos, rules of communication), resolving differences in team meetings. We will check interpretation within 7 days of data capture with the data collectors to ensure the correct meaning is captured. Next, the findings will be presented to the study nurse and peer leaders followed by presentation to ZAIMARA recipients for member checking.

**Cost data analysis**. The cost analyses will examine the costs of ZAIMARA with respect to HIV/STI acquisition, the net cost of the intervention to the health system adjusting for cost savings from STI reduction. We will explore HIV incidence where possible. We will conduct individual cost effectiveness (CE) analyses for all 3 STIs and assess the overall CE of ZAIMARA. In addition, we will conduct 2 supplementary analyses to estimate: (a) the CE of ZAIMARA when viewed strictly as an HIV prevention intervention; and (b) the CE with all 4 STIs (G, C, T, HIV) included.

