**Randomization**. We will randomize AGYW-MF dyads to one of two conditions (ZAIMARA or HP) following the baseline assessment (Fig. 1). We will use stratified permuted block randomization (blocks of 2) to ensure uniform distribution across arms and a balanced allocation (*n* = 300–325 ZAIMARA and *n* = 300–325 HP) throughout enrolment. AGYW and MF dyads will be randomized to the same condition. By stratifying the randomization process at the clinic level, we will account for potential variations in participant characteristics by neighborhood or clinic-specific factors, enhancing the validity and reliability of the study findings. Pre-determined randomization logs at each site will guide assignment to arms.

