**Fig. 1 Fig1:**
[figure not shown]
Flowchart for ZAIMARA intervention versus Health Promotion for AGYW-MF dyads

**Peer leaders**. Peer leaders (*N* = 60) will be female and live in the community where the program is delivered, have prior experience working with young people, have a minimum grade 12 education, and be proficient in reading and writing English and/or IciNyanja or ChiBemba. ZAIMARA and HP will be co-facilitated by four female peer leaders, each as follows: two peer leaders, ages 22–29 years-old will co-facilitate ZAIMARA to AGYW, and two peer leaders ages 30 years and older will co-facilitate ZAIMARA to MF. Likewise, two peer leaders ages 22–29 will co-facilitate HP to AGYW, and two peer leaders ages 30 years and older will co-facilitate HP to MF. Randomization will be stratified by clinic site, intervention arm, and age (22–29 years-old or ≥ 30 years-old).

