**Randomization.** We will randomize peer leaders to one of two conditions, mental health distress screening with referral (*n* = 30) or nutrition and exercise screening with improvement suggestions (*n* = 30) prior to the first workshop at the site but after the baseline assessment (Fig. 2). We will stratify peer leader randomization by treatment arm (ZAIMARA and HP) and age (22–29 years-old or ≥ 30 years-old) using predetermined block size.

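### The Aim 2 primary test leaves out the randomisation stratum and competes with a model whose covariates are picked by observed imbalance; the Aim 3 z-test is modestly miscalibrated at 30 v 30, and the peer-leader strata are described in three ways

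*Protocol article*

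**What the plan says.** **Aim 2 (dyads).** The Randomization paragraph stratifies by clinic in permuted blocks of 2 and gives the reason: "By stratifying the randomization process at the clinic level, we will account for potential variations". In Statistical analysis, Aim 2, the primary test is: "We will use a two-sided z-test with unpooled variance to test the inequality of the proportion of HIV testing uptake at 6-months". No stratum or covariate enters it. A log-binomial model then estimates the effect, "adjusting for potential confounders. Likelihood p-value < 0.05 will be considered statistically significant". The opening paragraph of Statistical analysis supplies the covariate rule: "We will adjust for potential confounders not balanced at baseline". It also allows random intercepts for clustering, including by site, but only where they turn out to be needed. For continuous secondary outcomes, "we will evaluate the effect of ZAIMARA using linear regression models"; no covariates are mentioned there.

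**Aim 3 (peer leaders).** The primary analysis compares job retention between the "mental health distress screening and referral versus nutrition and exercise screening groups using two-sided z-test with unpooled variance". The planned group sizes are 30 and 30. No expected retention is given.

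**Peer-leader strata.** The Peer leaders paragraph (after Fig. 1) says "Randomization will be stratified by clinic site, intervention arm, and age". The Aim 3 Overview says that randomisation is within site and arm. The Aim 3 Randomization paragraph says "We will stratify peer leader randomization by treatment arm (ZAIMARA and HP) and age", without site.

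**The concern.** Four things do not fit together.

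1. Clinic stratification is presented as the way the trial deals with site differences, but the primary test discards site. An unstratified analysis after stratified randomisation gives away some of the precision that the design bought.
2. A z-test has no likelihood p-value, so that significance sentence belongs to the log-binomial model. Two procedures then bear on the same hypothesis, and the text does not say which one decides if they disagree.
3. Choosing covariates after seeing which are imbalanced makes the adjusted estimate depend on chance and on an unstated threshold. It also selects on imbalance when precision comes from prognostic strength.
4. For Aim 3, a large-sample test is fixed for 60 people and an outcome whose proportion may be high. The strata that any analysis should reflect are described inconsistently.

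**Working it through.** **Reproducing the plan's own figure (Aim 2).** Inputs from the Sample size paragraph: control proportion 0.454, difference 0.12 (so 0.574), two-sided 0.05, 80% power, 270 per arm.

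- Sum of variances: 0.454 × 0.546 + 0.574 × 0.426 = 0.4924.
- n per arm = 0.4924 × (1.960 + 0.842)² / 0.12² = 268.4, so 269.
- Power at 270: SE = √(0.4924/270) = 0.0427; 0.12/0.0427 − 1.96 = 0.85; power 80.2%.
- Risk ratio: 0.574/0.454 = 1.26.

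The stated figure reproduces, with almost no power to spare.

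**Aim 2, cost of the chosen analysis.** The exact size of the unpooled z-test at 270 v 270 and 0.454 is 5.2%, so the test is sound. The comparisons below are simulations; the site and covariate rates are assumptions, because the article gives none.

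| Assumed setting | Analysis | Size | Power |
|---|---|---|---|
| Site rates about 25% to 65% | z-test without site | 4.2% | 81.6% |
| Same | Site-stratified Cochran-Mantel-Haenszel | 5.0% | 83.3% |
| Strong binary covariate (about 25% v 65%) | Unadjusted | 5.3% | 80.4% |
| Same | Adjusted only if imbalanced | 4.8% | 81.0% |
| Same | Pre-named covariate | 5.1% | 86.0% |
| Weaker covariate (about 35% v 55%) | Unadjusted / if imbalanced / pre-named | 5.1% / 4.9% / 5.0% | 80.6% / 80.9% / 81.6% |

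The imbalance rule recovers little of the available gain and does not inflate the error rate. With milder site differences (about 35% to 55%), stratifying by site makes no visible difference (80.8% either way).

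**Continuous secondary outcomes.** Including the baseline score multiplies the residual variance by 1 − ρ². For assumed ρ of 0.3, 0.5 and 0.7 this is 0.91, 0.75 and 0.51. At ρ = 0.5 the variance is 25% lower.

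**Aim 3, exact size at 30 v 30.** All pairs of binomial counts were enumerated for a common true retention, which is assumed.

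| Retention | 50% | 70% | 80% | 85% | 90% | 93% | 95% | 97% |
|---|---|---|---|---|---|---|---|---|
| Size of unpooled z-test | 5.2% | 5.8% | 6.0% | 5.9% | 5.5% | 4.4% | 2.8% | 1.0% |

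The size falls below 5% at about 92%. The matching 95% interval covers 92.6% of the time when retention is 0.95 v 0.85, and 94.2% when it is 0.90 v 0.80.

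**Aim 3, one possible result: 30/30 v 26/30.** The difference is 4/30 = 0.1333. The unpooled variance is 0 + (0.8667 × 0.1333)/30 = 0.00385, so SE = 0.0621, z = 2.148 and p = 0.032. Note that the group at 100% contributes zero variance. Boschloo's two-sided exact test gives p = 0.070 and Fisher's 0.11.

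**Peer-leader strata side by side** (60 leaders, 5 sites, 2 arms, 2 age groups).

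| Place | Factors | Cells | Average per cell |
|---|---|---|---|
| Peer leaders paragraph | site, arm, age | 20 | 3 |
| Aim 3 Overview | site, arm | 10 | 6 |
| Aim 3 Randomization | arm, age | 4 | 15 |

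These are three different schemes for one randomisation. Cells of 3 cannot split evenly and are too sparse for a regression term each.

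**The case against.** The strongest reply is that little is actually invalid. For Aim 2 the article uses the z-test to test and the model to estimate, which can be read as a natural hierarchy. An unstratified test after stratified randomisation remains valid and is, if anything, conservative. Random intercepts for site are provided for, and a condensed article may leave covariate lists to an analysis plan. The phrase about linear regression does not exclude a baseline score. Much of this stands. It limits the Aim 2 harm to precision and clarity, and it makes the baseline-score item a suggestion. It does not remove the imbalance rule, which is stated, or the separate significance rule attached to the model.

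Some stronger readings are tempting but unsupported:

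- *That imbalance-based adjustment inflates the type I error.* In simulation it gave 4.8% to 4.9%.
- *That two Aim 2 tests mean an inflated error rate.* If either were allowed to count, simulated error was 6.0% to 7.1% under the assumed covariates. The article does not say that either may count; it fails to say which does.
- *That the Aim 3 test produces excess false positives when retention is near 1.* There it is conservative. The excess lies between roughly 50% and 90% retention and is about one percentage point at most.
- *That the primary tests ignore a baseline value of the outcome.* Job retention has none, and the article lists no baseline HIV-testing measure.
- *That leaving site out of the peer-leader strata gives a definite chance of badly split sites.* That chance depends on block size, which is not published, and on the order in which sites enter. The Recruitment paragraph describes staged opening.

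**Conclusion.** The point holds as a change that should be made, not as a fatal flaw. For Aim 2 the z-test is valid at the planned size. The loss is under 2 percentage points of power from omitting site when sites differ widely, and up to about 5.6 points (86.0 − 80.4) from not pre-naming a strong covariate, both under assumed strengths. To this is added an adjusted analysis that is not fixed in advance and an unclear decider. For Aim 3 the miscalibration is modest in either direction, but the choice of test can move a plausible result across 0.05, and the interval can fall short of its nominal coverage. The Aim 3 size and coverage figures rest on assumed retention. The disagreement over peer-leader strata is a matter of text and needs no assumption.

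**What to change.** 1. **Aim 2 primary.** Name one deciding analysis: a risk-ratio model or a stratified test that includes site and a few prespecified prognostic baseline covariates already collected, such as age. Keep the z-test as supportive.
2. **Covariate rule.** Delete adjustment by observed imbalance.
3. **Continuous secondary outcomes.** Include site, and the baseline score where the outcome is measured at baseline.
4. **Aim 3 primary.** Replace the unpooled z-test with an unconditional exact test (for example Boschloo) and report a score or Newcombe interval for the difference.
5. **Peer-leader strata.** Reconcile the Peer leaders paragraph, the Aim 3 Overview and the Aim 3 Randomization paragraph to one scheme, bearing in mind that site by arm by age leaves about 3 leaders per cell.

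The cost is protocol and analysis-plan wording. No new data are needed. The one statistical price is slightly less power for Aim 3 with the exact test.

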## Intervention descriptions

**ZA****mbian**
**I****nformed**
**M****otivated**
**A****ware and**
**R****esponsible**
**A****dolescents and Adults (ZAIMARA)**. IMARA (see Table 1) was derived from three CDC-designated evidence-based interventions: SISTA (Sisters Informing Sisters about Topics on AIDS) [44], SiHLE (Sistering, Informing, Healing, Living, and Empowering) [45], and Project STYLE (Strengthening the Youth Life Experience) [46]. IMARA engages AGYW and their MF to address the individual, sociocultural, and structural factors that influence AGYW’s sexual behavior [32]. Ideally ZAIMARA is delivered in groups of 6 to 10 participants, with certain activities conducted separately for MF and AGYW, while others are implemented jointly. The separate MF and AGYW groups run simultaneously, covering parallel content. Joint activities are designed to enhance MF’s credibility as a resource for HIV/STI prevention and facilitate the practice of new skills. Additional activities focus on conflict negotiation, assertive communication, and strengthening the AGYW-MF relationship. The material is presented in a group format to promote structural change, build community norms for prevention, and reduce HIV stigma.

Beginning with an icebreaker and/or a national poem to enhance Zambian and gender pride, facilitators then review ZAIMARA’s goals. The program motto is presented to emphasize strong AGYW-MF relationships, foster sisterhood and community empowerment, build group cohesion, and increase motivation for HIV/STI prevention [47]. At the start of the workshop on day 1, each MF and AGYW signs the ZAIMARA pact to confirm their commitment to the program. ZAIMARA spans approximately 10–12 h, delivered over two days, ideally separated by one week to allow participants time to assimilate information. At the end of workshop day 1, MF and AGYW are given homework to complete before workshop day 2. ZAIMARA weaves in the impact of mental health issues and alcohol and drug use on HIV/STI risk (e.g., condom use while inebriated) throughout the curriculum.

**Table 1 Tab1:** Overview of ZAIMARA

Theory	Selected IMARA activities

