### Secondary outcomes

AGYW uptake of HIV testing at 12-, 18-, and 24-months. At 6-, 12-, 18-, and 24-months, AGYW PrEP uptake; HIV and STI incidence (gonorrhea, chlamydia, and trichomoniasis); Self-reported sexual behavior (e.g., condom use, substance use during sex, number of partners, concurrent partners) [48]. Standard cost evaluation methods [49, 50], including personnel time and non-personnel resources (e.g., travel expenses, snacks, incentives, curricular materials).

**Mediators and moderators**: At baseline, 6-, 12-, 18-, and 24-month follow-up: AGYW and MF reported HIV and STI knowledge [51], and PrEP knowledge and attitudes [52], parental acceptance and rejection in the AGYW-MF relationship [53], and quality and quantity of AGYW-MF communication [54–56]. AGYW will indicate their mental health and trauma exposure [57–60], substance use [61–63], and partner dynamics and communication [56, 64, 65].

**Sample size.** The sample size (*N* = 600–650 AGYW-MF dyads; *N* = 1,200–1,300 participants) was determined based on the primary hypothesis that HIV testing at 6-months will be higher among AGYW who receive ZAIMARA versus HP. Assuming 10% attrition at 6-months, we will have a sample size of *n* = 270 AGYW in ZAIMARA and *n* = 270 AGYW in HP. With at least 80% power, a 2-tailed significance level of 0.05, and the assumption of proportions in ZAIMARA and HP of 0.454 (null hypothesis), we will be able to detect a difference of 0.12 between the group proportions (equivalent to risk ratio = 1.26).

Effect sizes for binary outcomes is given in terms of the relative risk (RR), where RR = 1 indicates no treatment effect. A RR < 1 indicates a protective effect of the intervention. With 80% retention, we will have ≥ 80% power to detect RRs ≤ 0.38 when the proportion in the control group is 20%, and RRs ≤ 0.65 when the proportion in the control group is 50%. We calculated the standard effect size (*d*) in standard deviations for group mean comparisons with 80% power for continuous outcomes, where *d* = 0 is defined as no treatment effect. We will be able to detect a small to medium effect size (*d* = 0.36) even with 75% retention. Low HIV incidence among AGYW (2.54%) per year will allow us to explore incidence, but we do not expect sufficient statistical power to test intervention effects on HIV incidence.

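### Both programmes are delivered in groups, but the primary z-test and the 270-per-arm power figure assume independent girls, and adjustment for clustering is left conditional

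*Protocol article*

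**What the plan says.** The Randomization section allocates each dyad individually, stratified by clinic. Delivery is in groups: "Ideally ZAIMARA is delivered in groups of 6 to 10 participants", with some activities joint and some separate for mothers and girls. The health promotion control also meets in groups. The Peer leaders paragraph assigns two co-facilitators to the girls' group in each arm, and the Contamination paragraph states that peer leaders do not overlap between arms.

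Under Statistical analysis, Aim 2, the primary test is: "We will use a two-sided z-test with unpooled variance to test the inequality of the proportion of HIV testing uptake at 6-months". A log-binomial model then estimates the effect with adjustment for confounders; no cluster term is mentioned. The general paragraph above it says "We will use models with random intercepts to account for clustering (if needed) and test the significance of clustering", naming groups and sites as the levels. It does not say what makes adjustment needed, or whether a clustered model would then take over from the z-test.

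The Sample size paragraph reads "Assuming 10% attrition at 6-months, we will have a sample size of" 270 girls per arm. "With at least 80% power, a 2-tailed significance level of 0.05" and a proportion of 0.454, it concludes that "we will be able to detect a difference of 0.12 between the group proportions". It states no ICC, group size or design effect.

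**The concern.** This is an individually randomised group-treatment trial. After randomisation, girls in one workshop share sessions, peers and facilitators, and the group format is intended to shift shared norms. Outcomes within a workshop may therefore be correlated. Workshops and peer leaders are nested within arm, so variation between groups enters the treatment contrast directly, and blocking within clinic does not remove it.

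A two-sample z-test cannot carry that correlation. If the within-group ICC is positive, its standard error is too small, its type I error exceeds 5%, and the power figure is too high. At stake are the p-value and interval for the primary outcome and the claim of at least 80% power.

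Clinic is a different matter. It is a randomisation stratum present in both arms, so similarity within a clinic does not by itself inflate type I error.

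**Working it through.** **Inputs from the protocol.** Proportions 0.454 and 0.574 (difference 0.12); two-sided alpha 0.05; 270 analysed per arm after 10% attrition from 300; enrolment of 600 to 650 dyads; 16 to 20 dyads per round at a site, split over two arms.

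**Assumptions.** ICC 0.01, 0.02 and 0.05 (none is stated). Eight analysed girls per group: 8 to 10 enrolled per arm per round, about 9, less 10% attrition = 8.1.

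**Step 1: the stated figure.** Unpooled variance sum = 0.454×0.546 + 0.574×0.426 = 0.2479 + 0.2445 = 0.4924. SE = √(0.4924/270) = 0.0427. Power = Φ(0.12/0.0427 − 1.96) = Φ(0.85) = 80.2%. The required n is 269 per arm. The protocol's figure is reproduced with a design effect of exactly 1, leaving no margin at 270.

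**Step 2: allow for groups.** DE = 1 + (m − 1)×ICC. Type I error of the unadjusted z-test = 2×[1 − Φ(1.96/√DE)]. Power of a test with the correct variance = Φ(0.12/(SE×√DE) − 1.96). Example at ICC 0.05, m = 8: DE = 1 + 7×0.05 = 1.35; 1.96/√1.35 = 1.687, so the error is 9.2%.

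| ICC (m = 8) | DE | z-test type I error | Power, 270 per arm | Power, about 292 per arm | Analysed per arm for 80% (dyads enrolled at 10% attrition) |
|---|---|---|---|---|---|
| 0.01 | 1.07 | 5.8% | 77.5% | 80.6% | 288 (640) |
| 0.02 | 1.14 | 6.6% | 74.9% | 78.1% | 307 (684) |
| 0.05 | 1.35 | 9.2% | 67.7% | 71.1% | 364 (810) |

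The 292 column is 650 dyads: 325×0.9 = 292.5 per arm, with 83.2% power under independence. A beta-binomial simulation of the z-test (20,000 null trials per setting, m = 8) gave 6.0%, 6.9% and 9.6%, close to the formula.

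**Step 3: smaller groups.** If the 6 to 10 participants include mothers, there are 3 to 5 girls per group. With m = 4, DE is 1.03 to 1.15, type I error 5.4% to 6.8%, and power at 270 per arm 79% to 75%.

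**Step 4: if the conditional wording acts as a pre-test.** In the same simulation, a 5% heterogeneity test detected clustering in 10%, 19% and 58% of trials at ICC 0.01, 0.02 and 0.05. Switching to a cluster-level test only when that pre-test was significant gave an overall type I error of 5.7%, 6.0% and 6.2% (5.3% at ICC 0.10). Always allowing for clustering gave about 5.0%.

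**The case against.** The protocol does foresee clustering at workshop-group level and names a method for it. The sentence joins two actions without a decision rule, and a SAP that is not shown could supply one. The Aim 2 paragraph also plans a log-binomial model and refers to a likelihood p-value, which is model language; that model could take a random intercept. If a clustered analysis did replace the z-test whenever clustering was detected, the inflation would be about one percentage point.

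This limits the size of the point. A reader might infer that type I error will be close to 10%. The documents do not support that: the upper figures belong to a z-test that is never adjusted, at an assumed ICC of 0.05. A reader might also take the significance test of clustering as a written gate. That is a fair inference, but the rule is not stated. Nor should the low detection rate of a pre-test be combined with the error rate of a plan that has no pre-test; they describe different procedures.

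Two further limits stand. Similarity within a clinic, or within a round shared by both arms, largely cancels, so a total within-group ICC somewhat overstates the design effect. And the Missing data paragraph's expectation of at least 80% retention, against 10% attrition in the sample size, is a separate conflict; power at 240 per arm should not be charged to clustering.

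One possible defence fails. The secondary detectable effects (RR 0.38, RR 0.65, d = 0.36) correspond to roughly 118 to 122 per arm, as though a design effect near 2 had been applied. No such factor is stated, and the primary calculation contains none.

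What survives is that the protocol names an independence-based primary test and an independence-based power figure, and its only provision for groups is conditional.

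**Conclusion.** The point holds in direction for any positive within-group ICC; its size rests on assumptions. With ICC 0.01 to 0.05 and about 8 analysed girls per group, the unadjusted z-test runs at about 5.8% to 9.2%. Power is 77.5% to 67.7% at 270 per arm and 80.6% to 71.1% at about 292. The shortfall is minor at ICC 0.01, where enrolling all 650 dyads still keeps 80%, and smaller again with about 4 girls per group. It becomes material towards ICC 0.05. If adjustment works as a pre-test that really switches the analysis, type I error is only about 5.3% to 6.2% over ICC 0.01 to 0.10, although the pre-test would miss clustering in most trials at ICC 0.01 to 0.02. This is more than detail left to a SAP, because it concerns a test and a power figure that the protocol states.

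**What to change.** - Delete the 'if needed' qualifier, and do not let adjustment depend on a significance test of clustering.
- Base primary inference on the planned risk-ratio model with workshop group (site by round by arm) as the cluster in both arms. Use a random intercept, or robust standard errors with a small-sample correction. Keep clinic as a stratification factor. The z-test can remain as a descriptive comparison.
- Apply the same rule to the secondary outcomes.
- Restate power for 600 to 650 dyads with an explicit number of girls per group and an ICC range, and say whether the group size of 6 to 10 counts mothers.
- Record each dyad's workshop group in the data.

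The cost is a wording change and one extra data field. The downside is slightly wider intervals and a less favourable stated power.
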